**Exclusion criteria**

- a. Failure to provide informed consent form
- b. Not willing to return for follow up visits
- c. Physical impairment that would affect participation in physical activity
- d. Coming from outside Blantyre
- e. Patients classified as high risk for cardiac events during exertion

**Data management and analysis:** Descriptive analysis will be conducted using SPSS software; frequencies and mean changes with standard deviations and confidence intervals will be used to report the effect size of the intervention. Multivariate paired T tests will be conducted to compare the changes in each variable at the five time points, and **independent t-test will be conducted to compare the changes between the two groups.** Tables and graphs will be used to present the findings.

Expected outcomes: Participants in arm 1 will have better cardiovascular function and fewer hospital admission compared with the controls during the first 12 weeks and that these benefits will remain at 24 weeks.

**Dissemination plans:** Findings from the study will be presented to QECH management and clinicians involved in managing patients with CHF. The findings will also be presented at the COMREC dissemination conference. Furthermore, the results will be submitted to a peer review journal for publication.

***Anticipated challenges:*** It is anticipated that patients may be lost to follow up and discontinue with the prescribed intervention due to transportation related costs. Therefore, the patients enrolled in this program will be assisted with the transportation costs; patients enrolled will be those who will manage to travel the distance with the allowance given. In addition, patients will be asked to come for a therapy session at the hospital once each week and do the other two sessions at home with a trained family member.

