The sample size for this study is based on detecting the effect size (the difference between the groups) of 0.6 at 80% power with a two-tailed significance level of 0.05. Using the formula above, a total sample size of 40 was obtained for each group. Owing the attrition of dropout rates of 5%, the sample size required is 80 (40 on each arm). To avoid issues of bias in participant selection, all patients will be selected from the chest clinic at the hospital. According to the chest clinic records, both sexes and different adult age groups (usually 45 years and above) are presented on each clinic day. Numbers 1 and 2 will be put on small pieces of paper, which will be placed in sealed and unmarked brown envelopes. Each participant will be asked to pick one envelop that will determine to which group she or he will belong to; this will assist in avoiding the selection bias. In addition, to ensure that the sample size is reached, discussions will be done with the head of the chest clinic to schedule more patients with CCF within the study participants' enrolment period. According to the available recommendations worldwide, 10 patients are allowed to exercise using a circuit training approach for an hour, and 3-4 therapists must be available to supervise the program to ensure safety. Because access to the Physiotherapy department at QECH to implement this pilot intervention is in the afternoon (13:00-12:00pm), and the number of patients enrolled into the active Arm is 40, the College of Medicine Physiotherapy gym will be used; and therapy session will be every Wednesday from 8:30 am to 12:30 pm. Nevertheless, the Physiotherapy department at QECH will be actively involved in the care delivery of these patients at College of Medicine Physiotherapy gym throughout the study, for capacity building and to ensure continuity of care after the implementation of this study. The participants shall be recruited over a period of two months.

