While participants in the Arm 1 of the trial receive both treatment modalities of CR (counselling/education and exercise therapy) and their cardiologists' prescribed cardiac medications, participants in the Arm 2 will receive the prescribed cardiac medications and education about their condition (nature of disease, risk factor modification, compliance to medications, nutritional needs); participants in Arm 2 (the control group) will come at baseline, and after 4, 8, 12 and 24 weeks for assessment and education. Figure 2 illustrates the circuit training program that will be followed during the therapy sessions. The exercise session will start with a warm up session and end with a cool down session; both sessions will be done in a group. The Arm 1 participants shall be asked to carry out two therapy sessions for each week at home, and attend a session each week at the hospital. This will assist in reducing the travel costs and avoid losses to follow up. Nevertheless, supervision at home is essential to ensure safety of the patients and efficacy of the treatment at home. Therefore, one guardian for each participant will be trained on how they will supervise the therapy sessions at home. A one-day training for the guardians will be given. All patients will be given the same home-therapy program; box stepping, walking and jogging for a predetermined FITT based on each participants' exertion capacity. The intervention will be delivered over a 12 weeks' period; participants will visit the hospital once a week and perform the rest of therapeutic tasks at home on two extra days per week for the 3 months. After the twelve-week period, all participants will be followed up for a period of twelve more weeks. All COVID-19 preventive measures namely; hand hygiene, social distance and surface/equipment disinfection will be observed. Therapists will use surgical masks during exercise therapy sessions, and patients will be asked to put on the masks before and after the exercise therapy session because they may not be able to breath while exerting.

**Table 1.** The reference benchmark for exercise prescription

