#### **4.7 Data Collection**

A manual sphygmomanometer will be used to measure BP, Oximeter will be used to measure Oxygen saturations. PR will be checked manually by feeling the radial artery using the third and index fingers Risk stratification will be done using the BACPR stratification forms (Appendices 1-2). Exercise testing will be conducted using **Chester step test for prescription (Appendix 9)**, and **exertion tolerance capacity will be checked using 6-minute walk test**; more details on 6-minute walk test can be accessed using this link (<https://doi.org/10.1164/ajrccm.166.1.at1102>) (24), and outcomes of 6-minute walk test will be recorded using the form attached as an appendix (Appendix 3).

As aforementioned, patients will be screened at baseline before being enrolled into the CRP. At baseline, the following descriptive data will be collected; BP, PR, O2sats and exercise capacity.

Additionally, data on risk stratification for disease progression and occurrence of cardiac events during exercise therapy will be recorded at baseline. BP and PR will be checked before and after each session for safety purposes **(Appendix 12)**; patients will also be asked, on each hospital therapy day, about the challenges faced that may be negatively contributing to adherence of the home exercise and nutrition interventional advice given to be followed at home. All parameters, including incidents of hospital admissions, will also be examined and recorded at 4, 8, 12, 16 and 24 weeks. **The Physiotherapists will record challenges they experienced at all stages of this project; from enrolment of study participants to discharge (Appendix 11).** The data will be collected on paper, and transferred onto Microsoft excel sheet on a computer.

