## **6.0 Analysis and presentation of results**

The SPSS software will be used to analyze this data. Frequencies and mean changes with standard deviations will be used to descriptively illustrate the effect size of the intervention. Paired t-tests will be carried out to compare and show the changes in the variables at the start of the program and after 3 and 6 months of CR reception. **Independent t-tests will be carried out to compare results between the two groups.** Tables and graphs will be used to present the findings.

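### The protocol fixes an unadjusted t-test between arms, worded two ways, although baseline values are collected; separately, it names no primary contrast

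*Protocol*

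**What the plan says.** **Between-arm test.** Section 6.0: "Independent t-tests will be carried out to compare results between the two groups". Executive summary, data management and analysis paragraph: "independent t-test will be conducted to compare the changes between the two groups". Neither place mentions the baseline value, and neither says which variables or visits are compared.

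**Within-arm tests.** The executive summary has: "Multivariate paired T tests will be conducted to compare the changes in each variable at the five time points". Section 6.0 limits the paired tests; they are to "compare and show the changes in the variables at the start of the program and after 3 and 6 months of CR reception".

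**Data available.** Section 4.7: "At baseline, the following descriptive data will be collected", followed by blood pressure, pulse rate, oxygen saturation and exercise capacity. For follow-up: "All parameters, including incidents of hospital admissions, will also be examined and recorded at 4, 8, 12, 16 and 24 weeks". Section 4.5 gives the control arm no week-16 visit; its participants "will come at baseline, and after 4, 8, 12 and 24 weeks for assessment and education".

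**Sample size.** Section 4.4 is based on "detecting the effect size (the difference between the groups) of 0.6 at 80% power with a two-tailed significance level of 0.05", with sigma 1.2, 40 per arm and 5% dropout. It does not name the variable or visit that the 0.6 refers to, and no section names a primary outcome or a primary time point.

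**The concern.** There are two separate issues.

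**Efficiency and clarity.** A comparison of follow-up values and a comparison of changes are different estimators with different precision. Which is better depends on the correlation between baseline and follow-up. A model adjusted for the baseline value of the same variable is at least as precise as either, apart from a negligible loss of one degree of freedom. It also removes the need to choose. With about 40 per arm, a chance baseline difference carries into an unadjusted comparison of follow-up values.

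**Selection.** The sample size is for one test at 5%. The protocol measures several variables at several visits and ranks none. A nominally significant difference somewhere could then be presented as the trial's finding with no prior statement that it was the one of interest.

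**Working it through.** **1. The plan's own figure.** Section 4.4 states 40 per arm.

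- Printed formula and values: (0.9 + 0.84) × 2 × 1.2² / 0.6² = 13.9. With the z-sum squared: 24.2.
- Standard two-sided formula, 0.6 as a raw difference with SD 1.2: (1.96 + 0.84)² × 2 × 1.44 / 0.36 = 62.7, so 63.
- Standard two-sided formula, 0.6 as a standardised difference: (1.96 + 0.84)² × 2 / 0.36 = 43.6, so 44.

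None of these gives 40. That is a matter of its own. Here it means only that gains should be measured from the power actually available and shown under both readings of 0.6.

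**2. Inputs.**

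- Evaluable patients: 40 × 0.95 = 38 per arm (section 4.4).
- Standardised effect d: 0.6, or 0.6 / 1.2 = 0.5.
- Two-sided 5% level.
- Correlation r between baseline and follow-up: not given in the protocol; assumed 0, 0.3, 0.5 and 0.7.
- Assumed equal SD at baseline and follow-up, with the effect expressed in that single-occasion SD.

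**3. Formulas.** Variance relative to a follow-up comparison: follow-up 1; change 2(1 − r); baseline-adjusted (ANCOVA) 1 − r². Power is from the noncentral t with noncentrality d / √(relative variance) × √(n/2), on 2n − 2 degrees of freedom (2n − 3 for ANCOVA). Example for d = 0.6 and r = 0.5: ANCOVA effect 0.6 / √0.75 = 0.693, noncentrality 0.693 × √19 = 3.02, power 84.6%.

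| 38 per arm | r = 0 | r = 0.3 | r = 0.5 | r = 0.7 |
|---|---|---|---|---|
| d = 0.6, follow-up t-test | 73.3% | 73.3% | 73.3% | 73.3% |
| d = 0.6, change t-test | 44.7% | 58.8% | 73.3% | 91.5% |
| d = 0.6, ANCOVA | 73.3% | 77.2% | 84.6% | 95.1% |
| d = 0.5, follow-up t-test | 57.6% | 57.6% | 57.6% | 57.6% |
| d = 0.5, change t-test | 33.1% | 44.4% | 57.6% | 79.3% |
| d = 0.5, ANCOVA | 57.6% | 61.6% | 70.0% | 85.3% |

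The change test loses to the follow-up test below r = 0.5 and beats it above. The ratio of ANCOVA to change-score variance is (1 + r)/2, which never exceeds 1.

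**4. Family-wise error if every comparison were tested at 5%.** Under independence it is 1 − 0.95^k. The correlated figures are simulated with 40 per arm, assuming correlations of 0.5 to 0.8 between visits of one variable and 0.2 to 0.5 between variables.

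| Reading | Tests | Independent | Correlated (assumed) |
|---|---|---|---|
| 4 variables, 3 and 6 months | 8 | 33.7% | 23–31% |
| 4 variables, the 4 post-baseline visits listed for both arms | 16 | 56.0% | 32–49% |
| 5 variables (systolic and diastolic separate), 5 visits | 25 | 72.3% | 41–63% |

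The last row is the maximum. It splits blood pressure, which has a single row in Appendix 4, and it needs a week-16 visit that section 4.5 does not list for the control arm.

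**The case against.** **The two wordings may not conflict.** In section 6.0 the preceding sentences speak of changes, so *results* may be loose wording for the same thing. This stands: a reader might infer that two different estimators were deliberately specified, and the text does not show that. It does leave the estimator unsettled, and if changes are meant, the change t-test is the weaker choice at low correlation.

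**No 25-test plan is written.** A reader might infer that the between-arm test is to be repeated over all variables and five visits. The documents do not say so. The phrase about each variable at five time points belongs to the paired tests, and section 6.0 confines those to 3 and 6 months. What stands is narrower: the protocol sets no limit on the between-arm tests and names no primary one.

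**Adjustment and modelling are commonly left to an analysis plan.** That is a fair point for many details, but here the protocol itself names the test, and its cover letter presents the independent t-test as an essential addition. The text therefore needs changing.

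**This is a pilot with objectives worded as description, and the executive summary promises confidence intervals.** This softens the multiplicity point. It does not remove it: section 4.4 sizes the study as a hypothesis test, and the executive summary expects arm 1 to do better by 12 weeks and to keep the benefit at 24.

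**Conclusion.** The point holds in two separate parts.

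**Analysis choice.** The unadjusted t-test is valid under randomisation but inefficient, and its wording should be settled. At 38 per arm, adjustment gains over the follow-up t-test about 4, 11 and 22 percentage points of power at r = 0.3, 0.5 and 0.7 if 0.6 is standardised, and about 4, 12 and 28 if it is raw. Over the change t-test the gains are about 18, 11 and 4, or 17, 12 and 6. All of this rests on an assumed r; at r = 0 nothing is gained over the follow-up test. A fixed promise of extra power would go beyond the documents.

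**Primary contrast.** The sample size presumes one test and the protocol names none. The possible family-wise error spans 34% to 72% under independence, and about 23–31% to 41–63% under the assumed correlations, conditional on testing each comparison at 5%. A reader might credit the adjusted model with controlling this error. It does not; only naming one primary contrast in advance does.

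This is a worthwhile improvement, not a fault that invalidates the trial.

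**What to change.** 1. In section 6.0 and the executive summary, replace the independent t-test with one stated model that adjusts for the baseline value of the same variable: ANCOVA at each visit, or a mixed model over the visits that both arms attend (baseline, arm, visit, arm-by-visit). Report the adjusted arm difference with its 95% confidence interval. Use the same wording in both places.
2. Reconcile sections 4.5 and 4.7 on whether the control arm is assessed at week 16, so that the visits in the model are defined.
3. Name one primary variable and one visit before the data are seen. Six-minute walk distance at 12 weeks is a reasonable candidate: section 4.7 makes that test the measure of exertion tolerance, and the intervention ends at 12 weeks. The choice is for the investigators to confirm. Present the other variables and visits as estimates with confidence intervals, without claims of significance.

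The cost is about one paragraph of text. SPSS, already planned, fits both models, and no new patients, visits or measurements are needed.

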## **7.0 Dissemination of results**

The generated information will be presented to the multidisciplinary team involved in the care delivery to the cardiac patients at QECH. The findings will also be shared with the health care policies' key stakeholders during 2020 Malawi College of Medicine research dissemination conference. Furthermore, the results will be submitted to a peer review journal for publication.

## **8.0 Ethical issues**

Permission will be sought from the QECH director and heads of Physiotherapy and cardiac clinics. Informed consent (Appendices 5-8) will be sought from each patient before being enrolled into the

program. All patients will be screened for safety before implementing the exercise therapy. The data will only be accessible to the therapists involved in the delivery of this intervention and the investigators. All participants' transportation costs and time will be compensated on each hospital visit and will be given \$10 each

## **9.0 Anticipated challenges**

It is anticipated that patients may be lost to follow up and discontinue with the prescribed intervention due to transportation related costs. Therefore, the patients enrolled in this program will be assisted with the top-up transportation costs; patients enrolled will be those who will manage to travel the distance with the top-up allowance. This implies that patients enrolled in the study will be those coming from within Blantyre and immediate surrounding areas. In addition, the therapy sessions have been divided into two; one will be done at the hospital and two at home.

## **10.0 Requirements, timeline of events and budget**

**Table 2:** Required items for the execution of this study

| ITEM                                                                                       | ROLE/USE                                                                                                                                                                                                                                                                                                                                                                                                                  |
|--------------------------------------------------------------------------------------------|---------------------------------------------------------------------------------------------------------------------------------------------------------------------------------------------------------------------------------------------------------------------------------------------------------------------------------------------------------------------------------------------------------------------------|
| PERSONNEL: Physiotherapist
Cardiologist/physician
Statistician
Patients' guardian | To assess and deliver the intervention package
To refer patients for enrollment and respond to all relevant medical queries
To assist with data management and analysis
To guide and monitor home exercise treatment                                                                                                                                                                                             |
| Training: Physiotherapists & chest
medical team

Patients' guardian               | Briefing on the objectives of the study, the inclusion and exclusion criteria, the intervention package and their responsibilities. Testing the tools and intervention to evaluate the capacity of the health care workers to function effectively towards this study.

To equip them with knowledge and skills on how they can effectively guide and monitor a 2-day home exercise program every week for 12 weeks |
| Paper: 3 realms                                                                            | To print all checklists and reference guides, study information sheets, consent forms and to aide in the data management and report writing                                                                                                                                                                                                                                                                               |
| Transport: 1 or 2 tone                                                                     | To assist in transporting the equipment and all other accessories from the shop to the clinic site                                                                                                                                                                                                                                                                                                                        |
| Space: clinical gym area                                                                   | This will be in physiotherapy department at the hospital. The communication has been made already. In case emergency situations have occurred and the space is not conducive for our participants, we shall use COM physiotherapy clinical gym. The communication has also been made already and we have been assured of the space.                                                                                       |

|                                            |                                                                                                                                                                                   |
|--------------------------------------------|-----------------------------------------------------------------------------------------------------------------------------------------------------------------------------------|
| Participants' screening and assessment kit | A number of equipment and accessories (indicated in the budget) will be needed during the screening and assessment processes. These are items such as cones, timer, leaflets etc. |
| Exercise therapy kit                       | A list of equipment will also be needed for the delivery of the intervention. These are items such as treadmill, stepping boxes etc.                                              |

**Table 3:** Timeline of events

| ACTIVITY                                      | COMPLETION DATE   | RESPONSIBLE PERSON   | Key authority |
|------------------------------------------------------|--------------------------|-----------------------------|----------------------|
| Ethical approval                                     | September-October, 2020  | Investigators               | Investigators        |
| Site permission                                      | September-November, 2020 | Investigators               | Investigators        |
| Training and final discussions with all stakeholders | December, 2020           | Investigators               | Investigators        |
| Screening for enrollment                             | January-February, 2021   | Investigators               | Investigators        |
| Therapy implementation                               | February-March, 2021     | Investigator and therapists | Investigators        |
| Data management and analysis                         | April, 2021              | Investigators               | Investigators        |
| Report writing                                       | May-July 2021            | Investigators               | Investigators        |
| Dissemination of results                             | August-October, 2021     | Investigators               | Investigators        |

**Table 4:** Budget items for the study (1USD: 750MWK)

| ITEMS     | SPECIFICATION          | QUANTITY | COST PER ITEM                                          | TOTAL COST (MK) | TOTAL COST (\$) | JUSTIFICATION                                                                                                                                                                                     |
|-----------|------------------------|----------|--------------------------------------------------------|-----------------|-----------------|---------------------------------------------------------------------------------------------------------------------------------------------------------------------------------------------------|
| PERSONNEL | Cardiologist/Physician | 1        | MK20,000/session for 12 sessions                       | MK240,000       | \$320           | For medical enquiries, such as to do with medications. This will also be a focal person in all referrals into the study.                                                                          |
|           | Physiotherapists       | 4        | MK20,000/individual/session for 12 sessions            | MK960,000       | \$1280          | For enrollment, screening and implementation. Two therapists will be needed to conduct assessments on all patients during the follow up period at 16 and 24 weeks after the implementation period |
|           |                        | 2        | MK20,000/individual/session for 2 extra patient visits | MK40,000        | \$53.3          |                                                                                                                                                                                                   |
|           | Statistician           | 1        | MK20,000/day for 10 days                               | MK200,000       | \$266.67        | To assist with data management                                                                                                                                                                    |

|           |                  |                                |                                  |               |              |                                                                                                      |
|-----------|------------------|--------------------------------|----------------------------------|---------------|--------------|------------------------------------------------------------------------------------------------------|
| EQUIPMENT | sphygmomanometer | 3                              | MK30,000                         | MK90,000      | \$120        | 15 boxes will be given to the patients for home exercise program and 16 will be used at the hospital |
|           | Stethoscope      | 3                              | MK45,000                         | MK135,000     | \$180        |                                                                                                      |
|           | Dumbbells        | 18 pairs                       | MK12,000 a pair                  | MK 96,000     | \$128        |                                                                                                      |
|           | Stepping boxes   | 31                             | MK 17,000 a box                  | MK 527,000    | \$702.67     |                                                                                                      |
|           | Stair board      | -                              | Available                        |               |              | For strength training                                                                                |
|           | Thera-bands      | 3 (colored bundles: y, r, b) 1 | MK50,000 per bundle
MK800,000 | MK150,000     | \$200        |                                                                                                      |
|           | Treadmill        |                                |                                  | MK800,000     | \$1066.67    |                                                                                                      |
|           | Static bike      | 1                              | Available                        |               |              |                                                                                                      |
|           | Computer         | 1                              | Available                        | -             | -            |                                                                                                      |
|           | Kettle           | 1                              | MK20,000                         | -
MK20,000 | -
\$26.67 |                                                                                                      |
|           |                  |                                |                                  |               |              | To prepare tea for patients and therapists                                                           |

|          |                     |                      |                  |          |         |                                                                                                                                                                     |
|----------|---------------------|----------------------|------------------|----------|---------|---------------------------------------------------------------------------------------------------------------------------------------------------------------------|
| SUPPLIES | Disposable cups     | 40                   | MK2500/set of 20 | MK5,000  | \$6.67  | Needed for one session. Patients to bring own bottles for refill on all subsequent visits                                                                           |
|          | Paper               | 3 Realms             | MK15,000 each    | MK45,000 | \$60    | The listed items shall be needed as they are necessary for patients' hydration, hygiene and sanitation. In addition, the paper will be required for data collection |
|          | Tea                 | 2 packets            | MK2000 each      | MK4,000  | \$5.33  |                                                                                                                                                                     |
|          | Milk                | 3 tins               | MK4000 each      | MK12,000 | \$16    |                                                                                                                                                                     |
|          | Sugar               | 5 packets            | MK1000 each      | MK5,000  | \$6.67  |                                                                                                                                                                     |
|          | Hand soap           | 1 Litre              | MK 3500          | MK3500   | \$4.67  |                                                                                                                                                                     |
|          | Sanitizer           | 3 Litres             | MK 10,000        | MK10,000 | \$13.33 |                                                                                                                                                                     |
|          | Disinfectant        | 4 Litres             | MK 20,000        | MK20,000 | \$26.67 |                                                                                                                                                                     |
|          | Surgical face masks |                      | MK 32,000        |          | \$42.67 |                                                                                                                                                                     |
|          | Toilet paper        | 4 boxes              | MK 10,000 each   | MK32,000 |         |                                                                                                                                                                     |
|          |                     | 5 packets of 9 rolls |                  | MK50,000 | \$66.67 |                                                                                                                                                                     |
|          |                     |                      |                  |          |         | Personal protective equipment for both patients and health care workers.                                                                                            |

|                                     |                                         |                             |                  |                |               |                                                                                                                                                                 |
|-------------------------------------|-----------------------------------------|-----------------------------|------------------|----------------|---------------|-----------------------------------------------------------------------------------------------------------------------------------------------------------------|
| TRANSPORT                           | Vehicle

Fuel                     | Available

240 Litres | -
MK898/litre | -
MK215,520 | -
\$287.36 | Investigator to provide To
buy and collect the
necessities for the study
and to run all other
related errands.                                      |
| COMPENSATION
FOR
PARTICIPANTS | Transportation cost and
refreshments | 760 hospital
visits      | MK7500 per visit | MK5,700,000    | \$7600        | 15 Hospital visits for
each patient in arm 1
(40 participants), and 4
hospital visits for each
patient in arm 2 (40
participants).
Therefore, |
| CONTINGENCY                         |                                         |                             | MK200,000        | MK200,000      | \$266.67      |                                                                                                                                                                 |
| 10% COM
OVERHEAD FEES            |                                         |                             |                  | MK956,002      | \$1274.67     |                                                                                                                                                                 |
| TOTAL BUDGET COST            |                                         |                             |                  | MK10,516,022   | \$14021.4     |                                                                                                                                                                 |

This pilot study is being sponsored by NCT-BRITE.

